### Objectives of the study

2.2

Primary objective: To evaluate the effect of LED photobiomodulation on analgesia during labor as an alternative nonpharmacological intervention.

Research hypotheses:

Hypothesis 0 (null): the use of LED photobiomodulation exerts an analgesic effect similar to that of the bath therapy.

Hypothesis 1: the use of LED photobiomodulation exerts an analgesic effect superior to that of the bath therapy.

Hypothesis 2: the use of LED photobiomodulation exerts an analgesic effect inferior to that of the bath therapy.

Secondary objective: To evaluate fetal conditions using cardiotocography and the Apgar score in the first and fifth minutes after birth, and the level of satisfaction with the experience of childbirth using a questionnaire.

### Participants

2.3

The study participants will be women aged >18 years, who are expected go into natural labor in the Maternity Hospital of Mandaqui. The inclusion criteria for the study will be as follows: women who request analgesia during labor; nulliparous and multiparous women; women with term gestation; women without previous diseases, including diabetes, neurological diseases, and metabolic diseases; and women in whom it is possible to evaluate fetal vitality during analgesia.

The exclusion criteria will be as follows: women whose labor is induced with medications; women who request drug analgesia during labor; and women who undergo cesarean delivery.

The participants will be recruited on admission at the maternity hospital and will be randomized in the 2 study groups after clarifying regarding the study objectives and obtaining their informed consent.

The sample size has been estimated using the difference in means in the score of the VAS from a study that evaluated analgesia during labor.^[34]^ The difference in the mean VAS score between the groups was set as 2 (standard deviation: 1.6). The minimum number of participants considering a power of 80% and level of significance of 5% was 28, and the minimum number of participants per group considering possible exclusions was 30.

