## Introduction

1

Labor pain is one of the most severe and agonizing events in the life of a woman.^[1–3]^ In previous studies, approximately 41% of women have reported that the high level of pain during natural labor and the fear of pain were the most important reasons for choosing a cesarean section.^[4,5]^ Although pain is a common phenomenon during labor,^[6]^ analgesia for pain relief during labor may be necessary to ensure that labor occurs as naturally as possible,^[7]^ thus benefiting the fetus and the mother.

Labor pain can be controlled by pharmacological and nonpharmacological methods.^[1,4,6,7]^ The use of drugs is the most common method, particularly epidural analgesia.^[8,9]^ However, pharmacological methods may have side effects on the fetus and the mother.^[8,9]^

The administration of epidural analgesia interferes with the secretion of hormones involved in labor, such as oxytocin, prostaglandin-F2a, and β-endorphin;^[6,10,11]^ this interference increases the risk of side effects, such as hypotension, delays the progress of labor, and increases the need for cesarean delivery.^[6,12,13]^ The concern regarding the side effects of pharmacological methods and the philosophy of encouraging vaginal delivery have promoted the discussion pertaining to the existing nonpharmacological methods.

Nonpharmacological alternatives that have been shown to be effective in pain relief include Swiss ball exercises and the hot bath therapy.^[14–18]^ The authors of a systematic review have reported that the hot bath therapy reduced pain in women with a cervical dilation of 8 to 9 cm and therefore reduced the need for pharmacological analgesia.^[14,19]^ The authors emphasized that nonpharmacological methods are beneficial and presented few side effects and contraindications. Furthermore, nonpharmacological interventions are noninvasive and favor the active participation of the mother during labor.^[14,19]^

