Therefore, finding analgesic alternatives using effective nonpharmacological methods is an interesting challenge. Photobiomodulation is a noninvasive nonpharmacological intervention used for pain management in different areas of health sciences, such as orthopedics, physical therapeutics, dentistry, etc.^[20–23]^ Photobiomodulation therapy comprises the use of radiation sources, such as laser and light-emitting diodes (LEDs), for the application of nonionizing light; these radiations produce physiological benefits, such as increased microcirculation and ATP synthesis and decreased reactive oxygen species production.^[20–23]^

The analgesic effect of photobiomodulation occurs through the reabsorption of exudates, the elimination of algogenic substances, and via changes in the electrical conduction of the stimulus by maintaining the ionic gradient on both sides of the cell membrane, thereby avoiding or reducing depolarization. The effects of LED therapy on pain management, including the increase in blood flow and relaxation of spasms, have attracted the attention of professionals from different health sectors.^[24]^

The use of LED improves acute orthopedic conditions, such as sprains,^[24–26]^ postsurgical pain, cervical injury,^[27]^ upper and lower back pain, neck pain, and fibromyalgia.^[27–32]^ Because of the broad effects of photobiomodulation, LED therapy may be used as a nonpharmacological and noninvasive alternative for managing pain during labor and may provide comfort to the woman without producing any side effects.

The objective of this protocol is to evaluate the effect of LED photobiomodulation on pain management during natural labor compared with that of bath therapy. The second objective is to evaluate the fetal conditions at birth and in the first hours of life following LED photobiomodulation.

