**Table 1 T1:**
[figure not shown]
Schedule of enrolment, interventions, and assessments of treatments.

The participants will be randomized into 2 groups: intervention group [analgesia with LED therapy (n = 30)] and control group [analgesia with bath therapy (n = 30)]. The perception of pain will be evaluated using the visual analogue scale (VAS) with a score from 0 to 10 at baseline, that is, before the intervention. In both the groups, the procedure will last 10 minutes at each of 3 time points during labor: cervical dilation of 4 to 5 cm, 6 to 7 cm, and 8 to 9 cm.^[33]^ At the 3 time points, the level of pain will be assessed using VAS shortly after the intervention. Pharmacological analgesia will be promptly performed whenever necessary; in these cases, the participant will be excluded from the study and replaced with another consecutive participant.

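### Excluding randomised women who later have a cesarean breaks the comparison of pain and fetal condition, and can hide fetal harm

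*Protocol article*

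**What the plan says.** Section 2.3 (Participants) describes the population as women "who are expected go into natural labor in the Maternity Hospital of Mandaqui". On timing it says: "The participants will be recruited on admission at the maternity hospital and will be randomized in the 2 study groups", once consent has been given. The exclusion criteria in the same section end with "women who request drug analgesia during labor; and women who undergo cesarean delivery".

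For the first of those two groups, section 2.1 states the consequence: where drug analgesia is given, "the participant will be excluded from the study and replaced with another consecutive participant". No corresponding sentence is given for cesarean.

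Fetal condition is a secondary objective. Section 2.2 words it as "To evaluate fetal conditions using cardiotocography and the Apgar score in the first and fifth minutes after birth", and the Introduction also names fetal condition as the second objective. Sections 2.5.1 and 2.6 collect pain scores and cardiotocography after each session in both arms. No section says that women delivered by cesarean stay in the analysis.

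**The concern.** Mode of delivery is settled after allocation and often after one or more sessions. Excluding women on it conditions both the pain and the fetal comparison on something that happens after treatment has begun. The women left are those whose labor ended vaginally without drug analgesia, and that group need not be comparable between arms.

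The fetal objective is the more exposed. If an abnormal tracing can lead to a cesarean, the criterion takes out some of the deliveries that the objective exists to describe. The Discussion presents the trial as the first use of photobiomodulation for labor analgesia, so what it reports on fetal condition should not come from births selected by how they ended.

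**Working it through.** The protocol gives no cesarean rate, no indication for cesarean and no rate of fetal compromise, so there is no stated figure to reproduce. Its sample size rests on the VAS alone and does not bear on this point. The check has two parts.

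**Timing, from the text**

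1. Women enter expecting natural labor (2.3), so few should have a cesarean already planned. The criterion will mainly catch intrapartum cesareans.
2. Randomisation is on admission (2.3), before the mode of delivery is known.
3. The criterion has no time limit and stands beside drug analgesia, which 2.1 handles by exclusion after entry.
4. Section 2.3 also raises the sample size for possible exclusions, so losses after entry are foreseen.

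The natural reading is exclusion after randomisation.

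**Effect of the selection, on assumed rates**

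Let p be the true proportion with fetal compromise in an arm, c the probability of cesarean given compromise, and b the probability of cesarean without it. Among the women who remain:

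analysed rate = p(1 − c) / [p(1 − c) + (1 − p)(1 − b)]

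*Real harm, same cesarean practice in both arms* (p = 20% LED, 10% bath; b = 10%). For c = 50%:

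- LED: 0.20 × 0.50 / (0.20 × 0.50 + 0.80 × 0.90) = 0.10 / 0.82 = 12.2%
- Bath: 0.10 × 0.50 / (0.10 × 0.50 + 0.90 × 0.90) = 0.05 / 0.86 = 5.8%

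| c | LED | Bath | Risk difference (points) | Risk ratio |
|---|---|---|---|---|
| 10% | 20.0% | 10.0% | 10.0 | 2.00 |
| 25% | 17.2% | 8.5% | 8.8 | 2.03 |
| 50% | 12.2% | 5.8% | 6.4 | 2.10 |
| 80% | 5.3% | 2.4% | 2.9 | 2.18 |

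With b = 20%, the risk difference is 9.6, 7.0 and 3.2 points for c = 25%, 50% and 80%. With 30 women per arm and c = 50%, the expected numbers with compromise are 30 × 0.20 = 6 and 30 × 0.10 = 3, and half of each is removed.

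*No harm, same practice* (p = 10% in both arms, c = 50%, b = 10%): 5.8% in each arm. Both rates are too low, but there is no bias between arms.

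*No harm, practice differing by arm* (p = 15% in both, b = 10%): with c = 30% for LED and 60% for bath, the analysed rates are 12.1% and 7.3%. With the two values of c exchanged, the rates exchange too. A false signal can arise in either direction.

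*Absolute rate in a single arm* (separate assumed inputs: adverse finding in 3% of vaginal and 20% of cesarean births, cesarean rate k). Overall rate = 0.20k + 0.03(1 − k); share of events lost = 0.20k / overall rate.

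| k | Overall rate | Rate left after exclusion | Events lost |
|---|---|---|---|
| 5% | 3.9% | 3% | 26% |
| 15% | 5.6% | 3% | 54% |
| 30% | 8.1% | 3% | 74% |

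*Precision.* Even 0 events in 30 women leaves an exact upper 95% limit of 1 − 0.025^(1/30) = 11.6%.

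**The case against.** **It may be an entry criterion, or a matter for the analysis plan.** Induced labor, on the same list, can be known at entry, and the timing of each criterion is not spelled out. Against this, a cesarean in women expected to labor naturally is mostly not knowable on admission. An analysis plan could define who is analysed, but it cannot recover Apgar scores that were not collected because a woman had left the study. The objection leaves a need for clarification but does not remove the point.

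**A reader might infer that the safety comparison is biased towards no harm.** The documents do not support that. With equal true rates and equal practice there is no between-arm bias. With real harm and equal practice the risk difference shrinks but the risk ratio does not. Practice that differs by arm can push the result either way.

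**A reader might infer that data already recorded are deleted, or that women with a cesarean are replaced.** Neither is stated. Exclusion with replacement is written only for drug analgesia; extending the exclusion to cesarean is reasonable but remains an inference.

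**The link is not in the documents.** They do not say that fetal compromise leads to cesarean. The Introduction says of epidural analgesia, not of LED, that it "delays the progress of labor, and increases the need for cesarean delivery". The link is plausible and is used here as an assumption.

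**Fetal condition is secondary and imprecise anyway.** True: the 11.6% limit applies whether or not cesareans are kept. That limits what the fix can deliver but does not justify losing events.

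Two further readings also go too far. The Discussion says only that the method can serve as an alternative if outcomes are favourable, which is not a plan to recommend it. The Introduction's longer newborn horizon, "evaluate the fetal conditions at birth and in the first hours of life following LED photobiomodulation", is a separate matter and cannot be judged because Table 1 is not shown.

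**Conclusion.** The concern holds in a limited form. The criterion, as most naturally read, removes randomised women on an event after randomisation, and this breaks the randomised comparison for pain and for fetal condition. That conclusion rests on the text and needs no assumed rate.

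That the absolute fetal adverse rate is understated depends on compromise raising the chance of cesarean. Under the assumed rates above, the single-arm loss of events runs from 26% to 74%, and a true 10-point difference falls to between 8.8 and 2.9 points (b = 10%). These figures show what could happen; they are not estimates for this trial. The size and direction of any between-arm bias cannot be determined from the documents. What can be said is that harm could be hidden and that the comparison loses its protection.

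**What to change.** - Limit the criterion in section 2.3 to cesarean planned before randomisation.
- Keep women with an intrapartum cesarean in the trial and analyse them in their randomised arm, using cardiotocography and VAS up to the decision and the 1- and 5-minute Apgar scores.
- Report the cesarean rate and its indication by arm.
- Report fetal outcomes for all randomised women, with 95% confidence intervals.

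The cost is one reworded eligibility sentence and some extra abstraction from the delivery record. No treatment and no sample size changes. The drawback is a possibly less favourable safety table. The change should be made while these women's data can still be collected, since they may not be recoverable afterwards.

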#### Intervention group: LED therapy

2.5.1

LED therapy sessions will be held in the prelabor room. The patient who will undergo analgesia and the professional responsible for placing the LED plate on the patient's back, between T10 and L2, will be present at the time of the intervention. The LED plate will be covered with clear disposable polyvinyl chloride to avoid cross-contamination and ensure hygiene. During the interventions, the patient will be allowed to choose the position that is the most comfortable for her.

Three 10-minute LED applications will be performed when the patient has a cervical dilatation of 4–5, 6–7, and 8–9 cm. Data on the level of pain, characteristics of the membrane (intact or damaged), heart rate, cardiotocography, and uterine dynamics will be collected after each intervention.

The LED device used is SportLux (Cosmedical, São Paulo, Brazil), and the dose parameters are shown in Table 2.

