### Control group: bath therapy

2.6

The method of analgesia with the bath therapy will be performed using a hot shower at 37°C for 10 minutes. After showering the entire body or the back for 5 minutes, the participants will be allowed to direct the water flow to any area of the body that feels the most comfortable and to adjust the temperature themselves for improved comfort. Bath therapy will be performed at 3 time points during labor: at cervical dilatation of 4–5 cm, 6–7 cm, and 8–9 cm. Data on the level of pain, membrane characteristics (intact or damaged), heart rate, cardiotocography, and uterine dynamics will be collected after the bath therapy by performing the same measurements used in the intervention group.

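### Women are randomised on admission with no dilatation criterion, so a woman admitted past 5 cm is eligible for a three-session regimen whose first session she can no longer receive

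*Protocol article*

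**What the plan says.** **Entry (protocol article, section 2.3).** The target population is described thus: "The study participants will be women aged >18 years, who are expected go into natural labor in the Maternity Hospital of Mandaqui". The inclusion list contains "women who request analgesia during labor; nulliparous and multiparous women; women with term gestation", followed by absence of prior disease and the ability to assess fetal vitality. The exclusion list is "women whose labor is induced with medications; women who request drug analgesia during labor; and women who undergo cesarean delivery". Both lists are introduced as the criteria of the study, and neither uses cervical dilatation. On timing, "The participants will be recruited on admission at the maternity hospital and will be randomized in the 2 study groups", once the study has been explained and consent obtained.

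**Treatment and scoring (sections 2.1, 2.5.1 and 2.6).** Section 2.1 sets "3 time points during labor: cervical dilation of 4 to 5 cm, 6 to 7 cm, and 8 to 9 cm" for both groups, with a VAS score shortly after the intervention at each. Section 2.5.1 repeats this for LED: "Three 10-minute LED applications will be performed when the patient has a cervical dilatation of 4–5, 6–7, and 8–9 cm". Section 2.6 does so for the control: "Bath therapy will be performed at 3 time points during labor: at cervical dilatation of 4–5 cm, 6–7 cm, and 8–9 cm". Baseline VAS is defined only as the score before the intervention.

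**Withdrawal (section 2.1).** The one rule for excluding and replacing a participant after entry applies when pharmacological analgesia is given.

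**The concern.** The entry rule and the treatment schedule do not fit together. Dilatation does not go back, so a window that has passed at admission is lost. A healthy multiparous woman at term who arrives at 6 or 7 cm asking for pain relief meets every stated criterion. She is randomised, yet the first session and its VAS score are already impossible. The text does not say whether she should have been turned away, should be replaced, or should stay in with a partial regimen.

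What is at stake is what the trial can say about its own regimen. Some women would be allocated to three sessions and receive two or one for a reason that was known before randomisation. The earliest comparison would be missing for them by design. Their baseline pain would also be recorded later in labour than that of a woman who enters at 4 cm.

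**Working it through.** **Step 1. Set the entry rule against the schedule.**

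| Dilatation at admission | Eligible under 2.3? | Sessions still possible | VAS stages that can be scored |
|---|---|---|---|
| up to 5 cm | yes | 3 | 4–5, 6–7, 8–9 cm |
| 6–7 cm | yes | 2 | 6–7, 8–9 cm |
| 8–9 cm | yes | 1 | 8–9 cm |

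The 4–5 cm comparison would hold only women in the first row, the 6–7 cm comparison the first two rows, and the 8–9 cm comparison all three. The women compared change from stage to stage, and so does the number of sessions they have already had.

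**Step 2. Look for a rule that resolves it.** The exclusion criteria cover induction, drug analgesia and caesarean delivery. The replacement rule in section 2.1 covers pharmacological analgesia. Neither reaches a woman who is simply past the first window.

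**Step 3. Size.** The plan gives no figure for this point, and the share *p* of women admitted past 5 cm is not in the documents. I assume 10% to 30%. The other inputs are 30 women per arm, a difference of 2 and an SD of 1.6, all from section 2.3.

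- Women per arm who can be scored at 4–5 cm: 30 × (1 − p).
- Standard error of the between-arm difference: 1.6 × √(2/n).
- Power: two-sided *t* test at 5%, difference 2, SD 1.6.

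| p | n per arm | Standard error | Ratio to n = 30 | Power |
|---|---|---|---|---|
| 0 | 30 | 0.413 | 1.00 | 99.7% |
| 10% | 27 | 0.435 | √(30/27) = 1.05 | 99.5% |
| 30% | 21 | 0.494 | √(30/21) = 1.20 | 97.7% |

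Even at an assumed 50% (15 per arm) power is 91.0%. Loss of nominal power is therefore not the problem.

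**Step 4. Is the plan's stated minimum of 28 a usable threshold?** By the normal approximation, two-sided 5% and 80% power, n per arm = 2 × (1.960 + 0.842)² × 1.6² / 2² = 10.05, rounded up to 11. The *t*-test calculation gives 12. The stated 28 follows from these inputs neither per arm nor in total (22 to 24), so I do not use it to judge the loss.

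**Step 5. Bias or noise?** Dilatation at admission is fixed before allocation, so late arrivals are split evenly between arms in expectation. Chance imbalance remains possible. At an assumed share of 20%, the difference between arms in their number has a standard deviation of √(2 × 30 × 0.2 × 0.8) = 3.1 women.

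**The case against.** The strongest reply is that this is an inferred omission in a condensed article. Table 1, the schedule of enrolment and interventions, is not visible, and the full protocol may hold an entry window. The description of women expected to go into labour, and a first session at 4–5 cm in both arms, suggest that early entry was intended. Staff might well not randomise a woman who plainly cannot start the regimen.

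Part of this stands. A limit may exist in a document not shown, and the number affected is unknown. But section 2.3 gives what read as complete lists, and one of its criteria is a request for analgesia during labour, so arrival in established labour is within scope. The difficulty is a mismatch between two stated rules, not a missing detail.

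The reply is also right about harm, and three stronger readings should be set aside:

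- **That the LED-versus-bath comparison is biased.** Because dilatation at admission precedes randomisation, no between-arm bias is expected, and the 4–5 cm comparison among the remaining women is still randomised. Different timing of baseline adds noise only.
- **That the contrast is diluted because some women have had fewer earlier sessions.** Pain is scored shortly after each session, and nothing in the article says that the effect accumulates.
- **That a few late arrivals take the first stage below the required 28.** The text does not say whether 28 is per group, and the figure does not follow from its inputs, so falling below it shows no harm.

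**Conclusion.** The point holds as a mismatch between entry on admission without a dilatation criterion and a regimen whose first session is tied to 4–5 cm. Followed as written, the protocol admits women who cannot receive the three sessions, leaves them unscored at the first stage (or the first two), and gives no rule for them. The consequence is some loss of precision and a less clear answer about the three-session regimen, because each stage is compared in a different set of women.

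The size is conditional. At an assumed 10% to 30% of women past 5 cm at admission, the standard error at 4–5 cm is 5% to 20% wider, while power at the plan's own difference and SD stays at about 98% or above. This supports a cheap improvement to the plan. It does not support a claim that the trial is underpowered or its comparison invalid. It rests on the eligibility lists in section 2.3 being complete.

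**What to change.** Reconcile section 2.3 with sections 2.1, 2.5.1 and 2.6 as follows:

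1. Add to section 2.3: *cervical dilatation documented as no more than 5 cm at randomisation*. This is the upper edge of the protocol's own first window, and it changes no session or care.
2. Preferably, take consent on admission and randomise when the woman is in the 4–5 cm window.
3. Take the baseline VAS immediately before the first session. The upper limit alone would not make baselines comparable: a woman randomised at 1–2 cm and scored at that moment would have a baseline from well before her first session.

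The change removes failures that are knowable before randomisation. It does not guarantee all three sessions when labour is rapid, and women may still leave for drug analgesia or caesarean delivery.

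The cost is one eligibility line and a sentence on baseline timing, by amendment. Dilatation is already measured to time the sessions. Recruitment would be somewhat slower, and the trial would yield no data on women who arrive in advanced labour.

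### Eligibility rests partly on events that can follow randomisation, so women can be removed and replaced once their arm is known

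*Protocol article*

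**What the plan says.** Four statements in the protocol article bear on this point.

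- **Order of entry (2.3 Participants).** "The participants will be recruited on admission at the maternity hospital and will be randomized in the 2 study groups after clarifying" the objectives and obtaining consent. The population is women "who are expected go into natural labor in the Maternity Hospital of Mandaqui". Section 2.4 (Randomization) gives 1:1 allocation in blocks of 6 and no timing.
- **Inclusion (2.3).** The list has "women who request analgesia during labor; nulliparous and multiparous women; women with term gestation", and also "women in whom it is possible to evaluate fetal vitality during analgesia".
- **Exclusion (2.3).** Besides labour induced with medication, the list has "women who request drug analgesia during labor; and women who undergo cesarean delivery".
- **Handling after allocation (2.1, text under Table 1).** Pharmacological analgesia is given whenever needed, and "in these cases, the participant will be excluded from the study and replaced with another consecutive participant".

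The first session is at 4 to 5 cm of dilation in both arms (2.1, 2.5.1, 2.6). One arm receives an LED plate on the back, the other a hot shower.

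**The concern.** An eligibility criterion should be a fact that can be settled before allocation. A drug request and a cesarean can come at any time up to delivery. When such an event makes a randomised woman ineligible, an outcome is being used to decide who belongs to the trial.

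The two arms cannot be mistaken for each other, so the woman and the staff know the allocation when the removal happens. A request for drugs is plausibly a sign that the allocated method has not controlled the pain. Removing these women and filling their places takes the highest pain scores out of the arm that works less well. That arm then looks better than it is, and the t test or Mann–Whitney test in section 2.7 compares two selected groups.

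**Working it through.** **1. Can each criterion be settled at allocation, as the text stands?**

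| Criterion (2.3) | Known on admission? |
|---|---|
| Age, term gestation, previous disease | Yes |
| Labour induced with medication | Sometimes; it may already have started |
| Requests analgesia during labour | Only if she is already in labour and has asked |
| Fetal vitality can be evaluated during analgesia | Depends on reading: feasibility judged beforehand, or an observation during treatment |
| Requests drug analgesia during labour | Not finally; possible up to delivery |
| Undergoes cesarean | Only if planned; otherwise possible up to delivery |

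The exclude-and-replace rule in 2.1 confirms that removal for drug analgesia is meant to operate on women already in the trial.

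**2. The plan's own figures.** The article gives no exclusion rate. The nearest figure is the step from 28 to 30 participants for possible exclusions. If 28 is per group (the text does not say), the allowance is 1 − 28/30 = 6.7%. The 28 itself is not reproduced from a difference of 2, SD 1.6, 80% power and two-sided 5% (two-sidedness assumed): 2 × (1.960 + 0.842)² × 1.6² / 2² = 10.05, so 11 per group, or 12 with the t distribution. That is a separate matter and does not affect this point.

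**3. Randomisations needed for 60 retained women.** N = 60 / (1 − q), with the loss rate q assumed. For q = 10%, 20%, 30% and 40%, N = 67, 75, 86 and 100. This is a headcount and shows no bias in itself.

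**4. Illustration of bias, no true effect.** Inputs: SD σ = 1.6 (2.3) and 30 retained per arm (2.1). Assumed: normal scores; the fraction q of women highest on a driver of exclusion is removed and replaced; the driver has correlation r with VAS.

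- With c = Φ⁻¹(1 − q) and λ = φ(c)/(1 − q), the mean of the retained women shifts by −rσλ.
- Their variance is σ²[1 − r²(cλ + λ²)].

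Worked case, r = 1, 10% versus 40%:
- q = 0.10: c = 1.282, λ = 0.1755/0.90 = 0.195, shift −0.312, variance 1.823.
- q = 0.40: c = 0.253, λ = 0.3863/0.60 = 0.644, shift −1.030, variance 1.081.
- Bias = 1.030 − 0.312 = 0.72 points. Standard error = √[(1.823 + 1.081)/30] = 0.311. Noncentrality = 0.718/0.311 = 2.31, so the two-sided t test on 58 df rejects with probability 0.62.

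Bias in VAS points, favouring the arm that loses more women, followed by type I error:

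| Excluded | r = 0.5 | r = 0.8 | r = 1.0 |
|---|---|---|---|
| 10% vs 10% | 0.00; 0.05 | 0.00; 0.05 | 0.00; 0.05 |
| 10% vs 20% | 0.12; 0.06 | 0.20; 0.08 | 0.25; 0.11 |
| 10% vs 30% | 0.24; 0.09 | 0.39; 0.19 | 0.48; 0.32 |
| 10% vs 40% | 0.36; 0.15 | 0.57; 0.36 | 0.72; 0.62 |
| 20% vs 40% | 0.24; 0.09 | 0.38; 0.19 | 0.47; 0.35 |

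**5. The same mechanism with a true benefit of LED of 2 points.** Suppose r = 1 and every woman above one common pain level is removed. If the shower arm loses 20%, 30%, 40% or 50%, the LED arm loses 1.8%, 3.8%, 6.6% or 10.6%. The difference seen among the retained women is then 1.51, 1.34, 1.19 or 1.05 instead of 2. The bias can therefore hide a real effect as well as create a false one.

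**The case against.** The strongest reply concerns timing. Section 2.3 gives an order (recruitment, consent, randomisation) and no clock time. The Abstract describes the sample as women in labour, and section 2.1 describes them as requesting analgesia. The wording about women expected to go into natural labour may only mean labour that is neither induced nor ended by cesarean. Table 1, the schedule of enrolment and assessments, cannot be seen here and may place allocation later. A condensed article may also leave the exact moment to the full protocol.

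This stands in part: the text does not establish that women are randomised long before session 1. It does not remove the problem. Even with allocation at session 1, drug requests and unplanned cesareans can follow, and sections 2.1 and 2.3 would still remove those women.

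A second reply is that the figures above rest on assumed, unequal losses, and that equal losses leave type I error at 0.05. This stands. The figures show what the rule can do, not what it will do. They describe exclusion with replacement and do not measure any harm from randomising on admission.

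A third reply is that wanting analgesia and not asking for drugs are compatible conditions. This also stands, because the article separates pharmacological from nonpharmacological methods throughout.

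**Conclusion.** The point holds in limited form. As written, the plan makes eligibility depend in part on events that can follow allocation, and it removes and replaces randomised women on at least one of them (pharmacological analgesia) with the arm known. The comparison of those who remain can be biased in favour of the arm that loses more women. The amount cannot be derived from the article. Under the assumptions in the working it runs from nil (equal losses) to 0.72 VAS points with a type I error of 0.62. That the arms are open is inferred from the two interventions; the article does not use the word.

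A reader might infer more, and the text does not support it:

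- **That the criteria contradict each other.** Analgesia and drug analgesia are different terms, so a woman can meet both conditions. Separately, 2.1 says uniparous and 2.3 says nulliparous; that should be reconciled but has no bearing here.
- **That all three exclusions can only be seen later.** Induction already begun and a planned cesarean can be known before allocation.
- **That the baseline VAS is contaminated.** Section 2.1 says only that it precedes the intervention. Recording it after the arm is known is a possibility, not something the article states.
- **That later randomisation would remove most losses.** It prevents losses before session 1 and none after it.

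**What to change.** In sections 2.3 and 2.4:

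1. Obtain consent on admission. Confirm eligibility, record the baseline VAS, and randomise immediately before session 1.
2. Word the exclusions as states present before randomisation: labour already induced, drug analgesia already requested or given, cesarean already planned.
3. Here and in section 2.1, treat later drug analgesia and cesarean as post-randomisation outcomes. Do not replace these women; analyse them in their allocated group.

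Step 1 deals with losses before the first session; only step 3 deals with those after it. The clinical rule for giving pharmacological analgesia stays as it is.

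The cost is a few sentences of wording and an allocation procedure available on the ward at all hours. Keeping the women in the analysis also means stating how VAS scores after drug analgesia, or missing after a cesarean, are handled; that detail can sit in the analysis plan.
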